## Abstract

**Background:**

The approach-avoidance training program (AATP) has shown preliminary promise as an add-on to standard treatment for alcohol dependence. However, knowledge is lacking as to whether the effectiveness of AATP can be enhanced further when performed in a typical drinking situation. The main aim of this study is to investigate whether approach-avoidance training implemented in a virtual reality bar environment is superior to the classical joystick PC-version of the AATP.

**Methods:**

The study will be implemented as a randomized controlled trial. A total of 204consecutively enrolled alcohol use disorder (AUD) patients, recruited from alcohol inpatient clinics in Germany, Poland and Denmark, will be randomized into one of three groups at the start of standard alcohol treatment: group A) stimuli-relevant AATP + treatment as usual (TAU); group B) stimuli-relevant AATP in virtual reality + TAU, and group C) TAU only (control group). Treatment outcomes will be assessed at pre-treatment, post-treatment and 3-month follow-up. Repeated-measures ANOVA will be applied to compare the trajectories of the groups over time on drinking, craving and impulsiveness outcomes. It is hypothesized that the two experimental groups will achieve better treatment outcomes compared to group C and that group B will achieve better outcomes than group A.

**Discussion:**

This study is the first trial examining the effectiveness of stimuli-relevant AATP delivered in a VR environment. The use of VR has shown promise in enhancing the effectiveness of other psychological treatments and since AATP has already been shown effective as add-on treatment, it is of interest to investigate whether these effects can be further enhanced by implementing the program in more ecologically valid environments. If proven effective, the AATP-VR can, like the AATP, be implemented easily and cheaply as add-on treatment or continued care to enhance the effectiveness of current evidence-based treatment.

**Trial registration:**

ClinicalTrials.gov ID: NCT04283305

Registration date: 24.02.20

## Background

Alcohol use disorders (AUD) are associated with cognitive dysfunctions such as cognitive biases in the systems processing alcohol-related stimuli, which may play an important role in the maintenance of addictive behavior and impede the effectiveness of conventional evidence-based treatments [1–3].

Dual process models suggest that addictive behavior is influenced by two semi-independent cognitive systems: (1) a fast and automatic associative “impulsive system” that automatically evaluates stimuli in terms of motivational significance and triggers an approach or avoidance response based on this evaluation, and (2) a slow and controlled “reflective system” that regulates the automatic and implicit responses elicited by the impulsive system based on explicit and controlled higher cognitive processes [4–7]. It has been proposed that the impulsive system in addictive behavior is driven by cognitive biases: alcohol cues automatically capture attention (attentional bias) and elicit an approach action tendency (approach bias) promoting alcohol seeking and drinking behavior [8, 9]. AUD can be conceptualized as a dysfunction in both the impulsive and reflective systems. An over-activated impulsive system is sensitized and triggers cognitive biases towards alcohol cues, while a relatively under-activated and weakened reflective system is unable to regulate these biases. Because the impulsive system is partly automatic and implicit, biases towards alcohol cues in the environment lead to the maintenance of self-destructive drinking behavior despite explicit knowledge about the consequences generated by the reflective system [6, 7, 10].

Conventional evidence-based psychological treatments for AUD such as cognitive-behavioral therapy (CBT) rely mainly on the modification of reflective cognitive processes, while impulsive cognitive dysfunctions are addressed to a lesser extent and typically by applying cue exposure therapy (CET). During CET, patients with AUD are exposed to alcohol to elicit cravings while refraining from habitual approach action tendencies, that is, drinking behavior. With repeated exposure, the sensitization of the impulsive system is assumed to decrease over time. To date, CET has shown limited effects on alcohol consumption outcomes [11]. It has been suggested that this conventional method may not be effective because it fails to provoke cravings and approach biases when delivered in clinical settings, which is a pre-requisite for desensitizing the impulsive system [12, 13].

Novel psychological treatments targeting the impulsive system through the modification of cognitive biases are emerging building on experimental paradigms from clinical neuropsychology [14–16]. One approach targets attentional biases by training attention away from alcoholic cues and towards non-alcoholic cues [14, 15]. Another method targets approach biases by training approach action tendencies towards alcohol to react with avoidance action tendencies [16]. One treatment that has shown preliminary promise in clinical settings is the approach avoidance training program (AATP). This program builds on the diagnostic alcohol-approach-avoidance task (alcohol-AAT) [17, 18], which measures approach bias. During the alcohol- AAT, AUD individuals are requested to react to pictures of alcoholic drinks using avoidance responses (by *pushing* a joystick) and react to pictures of non-alcoholic drinks using approach responses (by *pulling* a joystick). Approach bias is indicated when reaction times are faster for approaching alcohol cues than for avoiding them, whereas the opposite indicates avoidance bias. The AATP is an attempt to modify approach biases for appetitive alcohol cues in sub-clinical and clinical AUD samples [16, 19–21]. During the AATP, patients are typically trained to ‘avoid’ alcohol and therefore requested to react to pictures of alcoholic drinks using avoidance responses (by pushing a joystick) and react to non-alcoholic drinks using approach responses (by pulling a joystick).

In contrast to other novel training programs targeting attentional bias [14, 15] and conventional CET methods [22–24], the AATP is more ‘embodied’ in that patients are requested to actively train action tendencies by reacting with pull vs. push motor responses (e.g. [25]). The AATP has shown promise in decreasing reaction times towards alcohol cues and alcohol consumption in sub-clinical and clinical AUD samples. In an initial experimental trial conducted on a subclinical sample of heavy drinking college students, it was found that those who were trained to avoid alcohol cues drank less in a taste test compared to those who were trained to approach alcohol [16]. In three subsequent clinical trials, AATP was found to be effective in retraining AUD patients to avoid rather than approach alcohol cues, and it was associated with a reduction in relapse rates [8, 19, 20]. Further, a study examining whether AATP could be successfully delivered to a sub-clinical AUD sample via a fully automated web-based delivery pathway also found a reduction in alcohol consumption [26]. In addition, it has recently been shown that AATP may be effective in reducing approach biases even when treating AUD individuals with major and severe alcohol-induced cognitive dysfunctions in the reflective system [27]. Interestingly, functional imaging studies have shown that the intervention decreases brain activity in neural correlates of automatic and implicit cognitive processing (mesolimbic brain regions), suggesting that AATP targets the neural mechanisms behind the maintenance of AUD [9, 21, 25, 28]. Overall, AATP interventions have to date shown better effect in reducing alcohol consumption than conventional methods targeting the impulsive system.

The use of virtual reality (VR) has shown some promise in enhancing the effectiveness of psychological AUD treatments targeting implicit and automatic cognitive processes. In clinical settings, adding VR to CET has been shown to be potentially more effective than conventional delivery methods when it comes to inducing cravings [12, 13]. Although AATP interventions have shown more clinical promise than CET in reducing alcohol consumption, it has been difficult to probe any reductions in craving levels [8, 19, 20, 26]. Adding VR technology simulates and enriches real-life situations by exposing AUD individuals to a wider range of stimuli than possible in clinical settings, which typically only expose AUD individuals to alcohol and not associated situations that can cause cravings and approach responses (e.g. bars and party environments) [13]. If conventional methods targeting the impulsive system can be improved using VR, an emerging question then is whether adding VR to AATP may enhance the effectiveness of this approach.

### Aims

The objectives of the study are to investigate: 1) whether AATP as an add-on to CBT increases the effectiveness of treatment, and 2) whether AATP delivered via VR as an add-on to CBT is superior compared to conventional ATTP.

## Methods/design

The study is registered according to the Standard Protocol Items: Recommendations for Interventional Trials (SPIRIT) guidelines [29] and trial registered: ClinicalTrials.gov ID: NCT04283305, the 24 of February, 2020 and will be conducted based on the CONSORT guidelines [30]. In there are any amendments during the trial, it will be registered on ClinicalTrials.gov.

### Design and setting

The study will be conducted as a multi-national, parallel investigator-blinded randomized controlled trial. Participating countries include Germany, Poland and Denmark.

A total of 204 consecutively enrolled AUD individuals (see Statistical analysis section for the power calculation) will be recruited from inpatient alcohol treatment (68 patients from each country). In each country, participants will be recruited at treatment entry from clinics primarily treating AUD or patients whose primary substance use disorder is AUD. Participants will be recruited from the University Clinic in Hamburg-Eppendorf (Germany), the Pomeranian Medical University Clinic in Szczecin and West Pomerania (Poland), and the inpatient clinic Ringården in Middelfart, Funen (Denmark).

### Treatment as usual at the inpatient alcohol clinics

In all three countries, treatment as usual (TAU) consists mainly of psychological treatment which in some cases is combined with pharmacological treatment in accordance with the NICE guidelines [31]. At treatment entry, the patient is offered detoxification (e.g. diazepam, lorazepam, oxazepam or clomethiazole), and other pharmacological treatment (e.g. acamprosate, naltrexone or disulfiram) is provided to support abstinence if needed. The psychological treatment consists mainly of CBT applied during hour-long individual or group sessions. In Germany, TAU lasts for approximately 1 month, whereas in Poland it lasts for approximately 2 months and Denmark it lasts for approximately 3 months. The inpatient treatment in Germany is shorter due to a shorter coverage of the health insurance. Although patients are encouraged to strive for abstinence, the treatment goal for some patients is moderate drinking, defined as not drinking more than five drinks per occasion. In all countries, the treatment strategy is planned together with the patient and typically incorporates psycho-education, functional analysis of drinking situations, development of coping strategies, problem-solving, and homework between sessions.

The psychological treatments are delivered by trained therapists encompassing nurses, social workers and psychologists. Supervision takes place frequently and psychiatrists and clinical psychologists monitor the treatment course regularly.

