### Measures

Socio-demographic factors, AUD diagnoses and severity, prior AUD treatment, psychiatric comorbidity, medication, behavioral inhibition and treatment goal will be assessed in the baseline interview (T1). Clinical outcome measures relating to alcohol consumption and cravings will be assessed at baseline, post-treatment, and 3-month follow-up (T1, T2, and T3). Additionally, experimental outcomes, including approach biases, cue-induced cravings and a response inhibition task, will be assessed at baseline and post-treatment (T1 and T2) (See Fig. 1 for an overview of the assessment and intervention timeline across countries). Finally, the patients will be assessed for concomitant treatment between the post-treatment and 3-month follow-up at the 3-month follow-up assessment (T3). The assessments will, like the interventions, be carried out by trained research assistants.

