### Statistical analysis

Descriptive statistics will be calculated to summarize socio-demographic factors, AUD diagnosis and psychiatric comorbidity as well as primary and secondary measures at baseline. Categorical variables will be described using frequencies and percentages. Normally distributed numeric variables will be described using the mean/standard deviation (SD), non-normally distributed numerical variables using the median/interquartile range (IQR).

The main analyses will be conducted with a repeated measures ANOVA, with group as the between-subjects factor and drinks per day the last 30 days at each assessment time-point as the within-subjects factor, to test the effectiveness of the intervention across the assessment points, which would be indicated by a significant Time X Study Group interaction. If there is an overall significant interaction effect between any one time-point and group, we will examine whether the change over time differs between the groups and the time-point using contrasts. Secondary analysis of continuous outcomes will be conducted with repeated measures ANOVA models, with group as the between-subjects factor and other alcohol consumption- (drinking days and drinks per drinking day), craving-, impulsivity- and depressive symptom outcomes as the within-subjects factor. In the case of unbalanced attrition in the randomization groups, mixed models will be applied instead of repeated measures ANOVA. Secondary analysis of dichotomous outcomes (e.g. relapse) will be conducted using mixed model logistic regressions. The analyses will be adjusted for the randomization stratification variable, site, as well as for the outcome values at baseline [48]. Since the study is a randomized controlled trial, other covariates are expected to be balanced across the randomization groups. Missing data will be handled using multiple imputation with changed equation (MICE) methods applying the non-parametric predicted mean matching (PMM) methods [49].

All analyses will be conducted as intention to treat as well as per protocol, and subgroup analyses will be conducted on patients who were successfully treated with conventional or VR-based AATP, defined as completing all six sessions. Further, moderation analyses of approach bias and using anti-craving medication on the treatment effect will be conducted for the primary and secondary outcomes.

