When performing the descriptive and inferential analysis, the researchers will be blinded to the experimental and control groups, and an external statistician will conduct the analysis. The significance level in the models will be set at 5%, and two-sided analyses will be conducted. Effect sizes will be reported in accordance with the statistical modelling. All analyses will be conducted using Stata 16.

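### Treatment goal (abstinence or moderate drinking) is recorded at baseline but left out of the drinking models, which gives up a modest, nearly free gain in precision

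*Protocol article*

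**What the plan says.** Three places in the protocol article bear on this.

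- **Treatment as usual at the inpatient alcohol clinics.** Patients are encouraged towards abstinence, but "the treatment goal for some patients is moderate drinking, defined as not drinking more than five drinks per occasion". The share of such patients is not given.
- **Measures.** Goal is a baseline item: "behavioral inhibition and treatment goal will be assessed in the baseline interview (T1"). According to Recruitment, the baseline interview comes before randomisation, so this is a true pre-randomisation covariate.
- **Statistical analysis.** The primary model is a repeated-measures ANOVA "with group as the between-subjects factor and drinks per day the last 30 days at each assessment time-point as the within-subjects factor", tested through the time-by-group interaction. The adjustment set is fixed: "The analyses will be adjusted for the randomization stratification variable, site, as well as for the outcome values at baseline". The reason for stopping there follows: "Since the study is a randomized controlled trial, other covariates are expected to be balanced across the randomization groups". Approach bias and anti-craving medication are named as moderators; treatment goal is not.

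Goal is therefore collected but has no stated role in any analysis of drinking.

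**The concern.** The two goals imply different expected drinking after discharge. A patient who succeeds at abstinence and one who succeeds at moderation have different expected values of drinks per day, the primary variable. Few baseline items are tied so directly to the endpoint.

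Expected balance is a sound reason to trust an unadjusted comparison. It is not a reason to forgo a prognostic covariate, because balance on average neither reduces the residual variance nor corrects the imbalance in the one sample drawn.

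Baseline drinks per day may not carry the same information. The TLFB at T1 describes the preceding 30 days, whereas goal describes intended drinking later.

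What is at stake is precision. The Power analysis aims only for a small additive effect at 3 months, which is also when goal has most room to act, since the pre- and post-treatment assessments take place in an inpatient setting.

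**Working it through.** **1. Reproduce the stated sample size.** Inputs from Power analysis: f = 0.17, α = 0.05, k = 3 groups, m = 3 time points, ρ = 0.40, ε = 0.60. For the within-between interaction:

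- λ = f²·N·m·ε/(1−ρ) = 0.0289 × 123 × 3 × 0.60/0.60 = 10.66
- df1 = (k−1)(m−1)ε = 2.4 and df2 = (N−k)(m−1)ε = 144
- Power is 0.810 at N = 123 and 0.799 at N = 120, so 123 reproduces.
- The article then adds 20 patients for site (143) and allows for attrition: 143/0.7 = 204.3, stated as 204.

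**2. Variance explained by goal.** The article gives neither the share p with a moderate goal nor the difference d in drinks per day (in within-goal SDs). Both are assumptions: p = 10–50%, d = 0.2–0.8.

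- R² = p(1−p)d² / [1 + p(1−p)d²]
- After adjustment, λ becomes 10.66/(1−R²), with N held at 123.

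| p | d | R² | λ after adjustment | Power | N giving the planned power |
|---|---|---|---|---|---|
| 10% | 0.2 | 0.0036/1.0036 = 0.4% | 10.70 | 0.811 | 123 |
| 30% | 0.5 | 0.0525/1.0525 = 5.0% | 11.22 | 0.831 | 117 |
| 50% | 0.8 | 0.16/1.16 = 13.8% | 12.37 | 0.868 | 107 |

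The last column is 123 × (1−R²), rounded up.

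**3. How the gain depends on the test.** Step 2 applies R² directly to the error term. Suppose instead that goal acts only at T3 and is unrelated to baseline drinking, with ρ = 0.40. The share in the middle case is then:

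- T3−T1 change: error variance 2(1−0.40) = 1.2, so 0.0525/1.2525 = 4.2%
- T3 adjusted for baseline: error variance 1−0.40² = 0.84, so 0.0525/0.8925 = 5.9%
- pooled interaction: goal contributes (2/3) × 0.0525 = 0.035 against 2 × 0.60 = 1.2, so 0.035/1.235 = 2.8%, which gives power 0.822

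The order of magnitude is unchanged. For the pooled interaction test, the step 2 figures lean to the favourable side.

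**4. Realised imbalance.** With 143/3 ≈ 48 analysed per arm, the SD of the chance difference in goal share between two arms is √(2p(1−p)/47.7). This is 6 percentage points at p = 10% and 10 at p = 50%. A 1-SD imbalance shifts a single-time contrast by that SD times d, which is 0.01 to 0.08 SD. The standard error of such a contrast is √(2/47.7) = 0.20 SD.

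**5. Validity.** A simulated three-arm one-way comparison with no treatment effect (48 per arm, p = 30%, d = 0.8, 20,000 runs) that ignored goal gave a type I error of 0.0499. The nominal level holds.

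**6. Form of the covariate.** The time-by-group test uses within-patient differences. A goal effect that is constant over time cancels out of them, so in complete data a goal main effect leaves that test unchanged. Only a goal-by-time term, or goal in a contrast at T3, can recover precision.

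**The case against.** The strongest reply is that adjusting for the stratification variable and the baseline outcome is a valid, prespecified choice that nothing in the article contradicts. That stands: this is a possible improvement, not an error.

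It can also be said that the gain rests on assumed inputs and may be close to nil. That stands too. Site and baseline drinking may absorb part of the goal effect, and a goal stated at T1 may have changed by T3, particularly in Denmark, where usual treatment alone lasts about 3 months. These points argue for modest expectations, not for omitting a variable that is already collected.

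Two stronger readings are tempting, and the article supports neither.

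- A reader might infer that omitting goal introduces imbalance or bias between the arms. It does not. Chance imbalance comes from randomisation whatever the model, and the test's standard error already allows for it, as step 5 of the working shows. An unlucky draw is random error, not a flaw of the design.
- A reader might infer that patients who keep to a moderate-drinking goal will be counted as relapsed. The article names relapse only as an example of a dichotomous outcome and does not define it, so there is no stated definition to fault.

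**Conclusion.** The point holds as one of efficiency. Goal is allowed to differ, is measured before randomisation, plausibly predicts drinks per day after discharge, and is excluded for a reason that supports validity but does not address precision.

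Over the assumed range the gain is 0 to 6 power points (0.810 to between 0.811 and 0.868), with 0.831 in the middle case, and somewhat less if only the pooled interaction is considered. The size rests on the assumed share and effect of goal, and on goal not being largely captured by site and baseline drinking. The primary comparison remains valid as planned.

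**What to change.** Before unblinding, prespecify T1 treatment goal (abstinence or moderate drinking) as follows:

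- in the primary drinks-per-day model and the secondary drinking models, as a covariate together with its interaction with time, or equivalently as a covariate in the baseline-adjusted 3-month contrast;
- in the logistic model for relapse, as a covariate.

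Replace the sentence that relies on expected balance with one that gives the reason for each covariate chosen.

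The cost is three degrees of freedom in the repeated-measures form (one for goal, two for goal by time), or one in the 3-month contrast. No new data, visits or patients are needed. Fixing this now also avoids a dispute over post hoc adjustment should the arms turn out to differ on goal.

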### Recruitment

After completing detoxification but prior to starting standard treatment, the patient will be briefly informed about the project and asked if he/she is willing to meet with a research assistant who will provide further information. If the patient agrees, the research assistant will provide him/her with written and oral information about the study. After obtaining informed consent, a baseline interview will be carried out. Patients fulfilling the eligibility criteria will be randomized to one of the three aftercare treatment groups described below.

